#### **7.3.9. Database Lock and Unlock**

Database lock is an important milestone in the clinical study process. The locking process and time shall be clearly documented. Locking is to cancel the permission to edit the database, so that the data cannot be edited by any account.

If any modifications are needed after the database is locked, an application must be submitted. The modifications can only be implemented after joint discussion and signature confirmation by the sponsor, data management personnel, medical personnel, and statistician. The reasons for unlocking the database should be recorded in detail.

## 8. Statistical Considerations

The safety evaluation, efficacy evaluation, PK evaluation, PD evaluation, immunogenicity evaluation, and other analyses of this study will be specified in detail in a separate SAP. The SAP will be finalized before database lock.

### 8.1. Sample Size Estimation

The sample size of this study is not based on statistical calculations. It is planned to enroll 40 SLE subjects, with 10 subjects in each of the 2 mg/kg, 4 mg/kg, 8 mg/kg, and 16 mg/kg dose levels. At each dose level, 8 subjects will receive CM313 and 2 subjects will receive placebo.

### 8.2. Analysis Sets

**Full Analysis Set (FAS):** It includes all randomized subjects who have received at least one dose of IMP.

**Per-Protocol Set (PPS):** It is a subset of the FAS, including all subjects in the study who complete treatment with IMP as required by the protocol, have no major protocol deviations, and have available efficacy endpoints, and do not affect the efficacy evaluation. The PPS should satisfy at least the following criteria:

- Meeting the inclusion criteria specified in the study protocol;
- Meeting no exclusion criteria specified in the study protocol;
- Receiving no medications or treatments that may affect the efficacy evaluation during the study;
- Good compliance.

**PK Concentration Set for the First Dose (PKCS1):** It includes all subjects who have completed the first dose of IMP and have at least one valid post-first dose concentration data.

**PK Parameter Set for the First Dose (PKPS1):** It includes all subjects who have completed the first dose of IMP and have at least one valid post-first dose PK parameter.

**PK Concentration Set for the Last Dose (PKCS2):** It includes all subjects who have completed all doses of IMP and have at least one valid post-last dose concentration data.

**PK Parameter Set for the Last Dose (PKPS2):** It includes all subjects who have completed all doses of IMP and have at least one valid post-last dose PK parameter.

**PD Set (PDS):** It includes all subjects who have received at least one dose of IMP and have one valid PD data.

**Immunogenicity Set (IMGS):** It includes all subjects who have received at least one dose of IMP and have one valid post-dose immunogenicity data.

**Safety Set (SS):** It includes all subjects who have received at least one dose of IMP.

The above analysis sets will be discussed and decided jointly by the principal investigator, sponsor, statistician and data management personnel in the blind data review meeting before database lock.

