### **3.8. Study Treatment**

#### **3.8.1. Investigational Medicinal Products**

The IMPs used in this study include CM313 and its placebo, both manufactured by Chengdu Kangnuoxing Biopharma, Inc.

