### **3.8.3.3. Unblinding**

In this study, after all data are entered into the database, unblinding will be performed after the blind data review, database lock, and finalization of the Statistical Analysis Plan (SAP), , and then the data will be submitted to the statistical analysis personnel for statistical analysis. The unblinding process will be performed by the principal investigator, statistician, IWRS party, sponsor or its representatives, and will be recorded accordingly.

In case of emergency unblinding by the investigator, the specific grouping information of the subject will be obtained through the emergency unblinding module of the IWRS. If emergency unblinding is required, the principal investigator and relevant sponsor personnel will be notified as far in advance as possible before unblinding the IMP. The specific treatment group information of the subjects can only be obtained after approval by the principal investigator. In case of failure to contact the sponsor before emergency unblinding, the sponsor must be contacted within 24 hours of unblinding. Once emergency unblinding is performed, the corresponding subjects are dropped out. The date and reason for unblinding the subject, and the procedure of unblinding should be documented by the investigator in the source document. If an AE occurs at population level or the study is interrupted for any reason, early unblinding may be performed with the mutual approval of the sponsor and the investigator.

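### Deciding the PK parameter sets in the blind data review would reveal allocation for most or all dosed subjects, which conflicts with the unblinding rule in section 3.8.3.3

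*Protocol*

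**What the plan says.** Protocol section 8.2 defines nine sets: FAS, PPS, PKCS1, PKPS1, PKCS2, PKPS2, PDS, IMGS and SS. One closing sentence says how all of them are settled: "discussed and decided jointly by the principal investigator, sponsor, statistician and data management personnel in the blind data review meeting before database lock". No set is exempted.

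The rule for PKPS1 is: "It includes all subjects who have completed the first dose of IMP and have at least one valid post-first dose PK parameter". For PKPS2 it is: "It includes all subjects who have completed all doses of IMP and have at least one valid post-last dose PK parameter". The concentration sets are looser; for PKCS1 the rule is: "It includes all subjects who have completed the first dose of IMP and have at least one valid post-first dose concentration data".

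Section 3.8.1 states: "The IMPs used in this study include CM313 and its placebo". Having received IMP therefore does not separate the arms. Having a PK parameter does, because section 2 defines the parameters as those of CM313 and section 3.9.2 names the CM313 blood concentration as the measured quantity.

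On timing, section 3.8.3.3 says "unblinding will be performed after the blind data review, database lock, and finalization of the Statistical Analysis Plan (SAP"). Section 8 adds: "The SAP will be finalized before database lock".

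**The concern.** The meeting is called blind and comes before unblinding. To settle PKPS1 and PKPS2 as defined, however, those present must know which subjects have a valid CM313 parameter. That list is close to the allocation list.

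The people who would see it are the principal investigator, the sponsor, the statistician and data management. In the same meeting they settle the PPS on terms that need judgement: what counts as a major deviation, which treatments may affect the efficacy evaluation, and what good compliance is. The database is still unlocked. The text fixes no order between the meeting and SAP finalisation, so the SAP may still be open too. A later statement that the PPS was decided blind could be challenged.

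The protocol recognises this kind of leak elsewhere. Table 1 (note 19) and section 5.3.5 withhold IgG, IgA, IgM and IgE results from the sites until unblinding. No similar protection is stated for CM313 concentrations, which point to the arm more directly.

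**Working it through.** **1. Planned numbers (section 8.1).** 4 levels × (8 CM313 + 2 placebo) = 40, which reproduces the planned total: 4 × 8 = 32 CM313 and 4 × 2 = 8 placebo. Section 3.1 makes 16 mg/kg optional. Without it, 3 × 10 = 30 (24 CM313, 6 placebo).

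**2. Who can enter each PK set.**

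| Set | Requirement | CM313 recipient | Placebo recipient |
|---|---|---|---|
| PKPS1, PKPS2 | at least one valid PK parameter | yes | no CM313 exposure to derive one from |
| PKCS1, PKCS2 | at least one valid concentration | yes | possibly, if a below-quantification result counts as valid |

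Counting a Cmax of zero as a valid parameter does not fit section 8.3.5. The Power Model there uses log-transformed parameters, and zero has no logarithm. Nearly every CM313 recipient who completes the first dose should have a parameter: section 1.3.2 reports a mean first-dose Cmax of 42.397 µg/mL at 2 mg/kg, the lowest level here (3 myeloma patients).

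**3. What the PKPS1 list shows within one level.** Knowing only the 8:2 split, the meeting faces C(10,2) = 45 possible allocations. If k of the 8 CM313 recipients are not in PKPS1, then 2 + k subjects are outside it. C(2+k, 2) allocations remain, and each subject outside is placebo with probability 2/(2+k).

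| k | Allocations left | P(placebo, if outside) |
|---|---|---|
| 0 | 1 | 1.00 |
| 1 | 3 | 0.67 |
| 2 | 6 | 0.50 |

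Every subject inside the set is known to be on CM313, whatever k is.

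**4. Sensitivity.** The protocol does not give the share q of CM313 recipients who will lack a parameter, so q is an assumption, with subjects taken as independent. The chance that a level is fully readable from PKPS1 alone is (1 − q)^8. The expected share of all 40 subjects known with certainty to be on CM313 is 32(1 − q)/40.

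| q | Level fully readable | Share certainly CM313 |
|---|---|---|
| 0% | 1.00 | 0.80 |
| 2% | 0.85 | 0.78 |
| 5% | 0.66 | 0.76 |
| 10% | 0.43 | 0.72 |

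Reading PKCS1 beside PKPS1 can narrow what is left. A placebo recipient whose below-quantification results count as valid is in PKCS1 but not PKPS1. A subject who did not complete the first dose is in neither.

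**5. Weight of one PPS exclusion.** 1/8 = 12.5% of a CM313 group. For placebo it is 1/2 = 50% if summarised by level, or 1/8 = 12.5% if all 8 are pooled. The protocol does not say which.

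**6. The two rules together.** If PK parameters are available at the meeting, section 8.2 can be followed but allocation is visible before the point set in section 3.8.3.3. If they are not available, section 3.8.3.3 is respected but PKPS1 and PKPS2 cannot be decided as section 8.2 requires.

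**The case against.** The strongest reply is that nothing in the protocol puts PK results before the meeting. Section 7.3.8 describes the data review meeting without mentioning them. Section 5.4.2 sends the samples to a central laboratory. Section 8.3.5 makes the parameters part of the analysis, and section 3.8.3.3 hands data to the analysts only after unblinding. On that order, the PK sets might be settled at the meeting from doses given and samples taken, with the details left to the SAP.

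It is true that no release of PK results is stated, so disclosure follows from applying section 8.2 and is not itself a planned step. But the membership rule asks for a valid parameter, not for doses and samples. The protocol itself fixes the forum, the attendees and the time, so an SAP that said otherwise would contradict it.

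Other limits stand in full:

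- A reader might infer that the meeting could read off every subject's arm. That holds only if every CM313 recipient has a parameter; a subject who did not complete the first dose cannot be classified with certainty from the list.
- A reader might infer that all the PK and immunogenicity sets reveal the arm. PKCS membership need not, and IMGS needs only one valid post-dose immunogenicity result, which a placebo recipient can have.
- Section 8.3 ties no named analysis to the PPS.
- Section 3.1 lets the investigator and sponsor use PK parameters when discussing added dose levels and states no firewall. If those are subject-level data, amending section 8.2 alone would not protect the blind.

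**Conclusion.** The contradiction is in the protocol's own text and should be corrected. Applied as written, section 8.2 would reveal allocation for most or all subjects who completed the first dose. With every parameter available that is all 40 (or 30 without the optional level). With 10% of CM313 recipients lacking one, an expected 72% of subjects would still be known with certainty to be on CM313. This rests on two premises: that a placebo recipient has no valid CM313 parameter, and that the meeting applies the stated membership rule.

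A reader might go further and infer that the trial's conclusions are biased. The documents do not support that. The primary endpoint is safety, and the Safety Set takes in everyone dosed without discretion. Efficacy is exploratory, summarised descriptively and by Kaplan-Meier, with no between-group test specified. What is at risk is the credibility of the PPS decisions and of any claim that the data review was blind.

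**What to change.** Amend section 8.2 in two respects.

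- The blind data review decides FAS, PPS, SS, PDS and IMGS, and subject-level CM313 concentrations and PK parameters are withheld from that meeting.
- PKPS1 and PKPS2, and also PKCS1 and PKCS2 because validity there depends on concentration results, are assigned by validity rules written before unblinding. Assignment takes place after lock and unblinding, or is done by a firewalled pharmacokineticist who does not attend the meeting.

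Writing the validity rules beforehand matters because section 8.2 does not define what is valid, and leaving that open until allocation is known would create a new weakness.

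The cost is a few sentences and slightly later finalisation of the PK sets. Visits, sampling and treatment are unaffected.

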### **8.3. Statistical Analyses**

#### **8.3.1. General Principles**

Continuous variables will be summarized by mean, median, standard deviation, maximum and minimum; categorical or ordinal variables will be summarized by count and percentage.

All statistical analysis will be performed using SAS v9.4 statistical software.

#### **8.3.2. Subject Disposition**

The number of subjects who have been screened, have failed the screening, have been randomized into each dose level, completed treatment, and completed the study, as well as the number of subjects included in each analysis set will be summarized. Separate analyses will be conducted on the reasons for premature treatment discontinuation and withdrawal from the study.

#### **8.3.3. Demographics and Baseline Characteristics**

Descriptive statistics will be used to summarize demographics and baseline characteristics.

#### **8.3.4. Efficacy Evaluation**

Descriptive statistics will be performed on the SELENA-SLEDAI score, PGA score, prednisone dosage, BILAG-2004 score, 24-hour urine protein quantification (only for subjects with urine protein/creatinine ratio exceeding the ULN during screening), urine protein/creatinine ratio (only for subjects with urine protein/creatinine ratio exceeding the ULN during screening), and their changes from baseline, as well as immunology-related endpoints, CRP, ESR, and their percentage change from baseline at each visit after treatment for each group.

The Kaplan-Meier method will be used to estimate the first-flare rate of SLE at different time points in each group, as well as the 25th percentile, median, and 75th percentile of the time to first-flare of SLE and their 95% confidence intervals (Brookmeyer-Crowley method). Kaplan-Meier survival curves will also be plotted.

### **8.3.5. Pharmacokinetic Evaluation**

Descriptive statistics of serum concentrations at different time points for each dose level will be performed by the scheduled sampling time points, including the number of subjects, arithmetic mean, standard deviation, coefficient of variation, median, minimum, maximum, geometric mean and geometric coefficient of variation. Linear as well as semi-logarithmic plots of mean serum concentrations over time should be plotted for each dose level by scheduled sampling time points. Linear as well as semi-logarithmic plots of serum concentrations over time should be plotted for individual subjects by actual sampling time points.

PK parameters after the first dose and the last dose will be calculated using a non-compartmental model. Descriptive statistics will be performed for each PK parameter at each dose level.

The dose linearity of  $C_{max}$ ,  $AUC_{0-t}$ , and  $AUC_{0-\infty}$  (for the last dose only) will be assessed using the Power Model for the first dose and the last dose, respectively. A linear regression model will be fitted using log-transformed PK parameters as dependent variables and log-transformed doses as independent variables, and the slope and its 90% confidence interval (CI) will be estimated.

### **8.3.6. Pharmacodynamic Evaluation**

Descriptive statistics will be performed on the PD endpoints at each evaluation time point after treatment in each group, as well as their changes and percentage changes from baseline.

### **8.3.7. Immunogenicity Evaluation**

Descriptive statistics will be performed on ADA results at each evaluation time point for each group, and the number and percentage of ADA positive subjects in each group will be calculated.

### **8.3.8. Safety Evaluation**

#### **8.3.8.1. Drug Exposure**

Descriptive statistics will be performed on study duration, treatment duration, times of administration, and compliance, and compliance will be summarized categorically by <80%, 80%-120%, and >120%. Among them, study duration and exposure duration are calculated as follows:

Study duration (days) = date of study completion - date of signing the ICF + 1, where the date of withdrawal will replace the date of study completion for subjects who withdraw from the study early.

Treatment duration (days) = (date of last IMP injection - date of first IMP injection) + 1 day.

Compliance will be calculated by drug exposure, i.e., compliance = (actual total dosage / planned total dosage) × 100%.

#### **8.3.8.2. Adverse Events**

AEs will be coded using the Medical Dictionary for Regulatory Activities (MedDRA) and classified by SOC and PT. The analysis of AE in this study will mainly focus on TEAEs (defined as any AE that newly appears after treatment, or any AE that is present before treatment but worsens in severity after treatment). AEs that occur before treatment will be listed. Drug-related is defined as the relationship of an AE to IMP as "definitely related", "probably related", or "possibly related".

The number of events, number of subjects, and percentage of the following AEs will be calculated for each group by SOC and PT: all TEAEs, IMP-related TEAEs, severe TEAEs, IMP-related severe TEAEs, SAEs, IMP-related SAEs, TEAEs leading to treatment discontinuation, IMP-related TEAEs leading to treatment discontinuation, TEAEs leading to early withdrawal, IMP-related TEAEs leading to early withdrawal, TEAEs leading to death, and IMP-related TEAEs leading to death.

#### **8.3.8.3. Laboratory Tests**

Descriptive statistics will be performed for laboratory results in the form of shift tables to compare baseline and post-baseline results (based on the normal range and investigator's judgment of clinical significance).

#### **8.3.8.4. Vital Signs**

Descriptive statistics will be performed on vital sign variables and their changes from baseline at each post-treatment evaluation time point in each group.

#### **8.3.8.5. Physical Examination**

Descriptive statistics will be performed for physical examination results in the form of shift tables to compare baseline and post-baseline results (based on investigator's judgment of clinical significance).

#### **8.3.8.6. 12-lead ECG**

Descriptive statistics will be performed for 12-lead ECG findings in the form of shift tables to compare baseline and post-baseline results (based on the normal range and the investigator's judgment of clinical significance).

#### **8.3.9. Subgroup Analysis**

No subgroup analysis is planned for this study.

#### **8.3.10. Interim Analysis**

No interim analysis is planned for this study.

#### **8.3.11. Multiplicity Issues**

Multiplicity issues are not addressed in this study.

#### **8.3.12. Handling of Missing Data**

The rules for handling missing data in the efficacy data of this study are detailed in the SAP. Missing data in PK, PD, immunogenicity, and safety data will not be handled.

### **9. Quality Control and Assurance**

#### **9.1. Monitoring**

The sponsor has a moral, legal, and scientific obligation to ensure that the study is conducted in accordance with established study guidelines, GCP guidelines, applicable regulatory requirements, and regulations. As a coordinated measure to fulfill these obligations, in the study, the sponsor's monitor or his/her representative should visit the study site on a regular basis, in addition to frequent telephone and written communication with the study site. In order to assess subject enrollment, protocol compliance, completeness and accuracy of CRF entry, validation of CRF data and source documents, and occurrence of AEs, on-site monitoring, telephone inquiries, and periodic CRF reconciliation will be performed. The investigator must provide the monitor with access to all source materials and study documents.

The study site must complete the CRF in a timely manner and allow periodic reconciliation by the study monitor.

#### **9.2. Audit and Inspection**

Site audits may be conducted by the sponsor or its representatives. Audits include, but are not limited to, IMP supply, completeness of required documents, informed consent process, and

consistency of eCRFs to source documents. The investigator agrees and participates in audits conducted in a reasonable manner and at a reasonable time.

Sites may be inspected by regulatory authorities during or after the end of the study. Once an inspection has been performed, the investigator should contact the sponsor/CRO immediately. The investigator should fully cooperate with the inspection performed at a reasonable time and in a reasonable manner.

The purpose of the audit is to confirm that the study is accordance with ethical, regulatory and quality requirements.

### **9.3. Quality Control**

All personnel participating in the study should be trained regarding the protocol prior to the start of the clinical study. The investigators should read and understand the contents of the study protocol, understand the principles of GCP, unify recording methods and judgment standards, and strictly follow the protocol.

Quality control must be performed by qualified designee. Quality control will be performed at participating sites during the study. If special problems are identified in some sites, corrective actions should be established.

## **10. Ethics**

### **10.1. Ethics Committee**

This study will be conducted in accordance with EC, GCP, ICH-GCP E6 (R2) guidelines and in compliance with applicable regulatory and data protection requirements.

Written, dated approval/favorable comment of the EC for protocol/protocol amendments, ICFs, other updated ICFs, subject recruitment process (e.g., recruitment advertisements), and other written materials provided to subjects must be obtained prior to the initiation of the study. In the EC approval letter, the version number of the protocol and the name of each document reviewed should be specified.

The EC shall keep all records of ethical review, including its written records, information of members, submitted documents, meeting minutes and relevant correspondence, etc. All records should be retained for at least 5 years after the end of this clinical study. The investigator, sponsor or drug regulatory authority may request the EC to provide its standard operating procedures and a list of ethical review members.

### **10.2. Ethical Guidance for the Study**

This study will be conducted in strict compliance with the protocol, the Declaration of Helsinki, GCP, ICH-GCP E6 (R2), and all other applicable laws and regulations.

### **10.3. Informed Consent of the Subjects**

The investigator will explain the benefits and risks of study participation to each subject, the subject's guardian, or an impartial witness, and obtain the written informed consent. Written informed consent must be obtained before the subject enters the study and any study-related procedures are conducted, including the use of IMP.

The original ICF signed and dated by the subject or his/her guardian and the relevant person conducting the informed consent discussion will be retained by the investigator as the study data. The investigator will provide the signed ICFs to all subjects.

During the study, the ICF may be revised after new and important data related to subject safety become available. In this case, EC approval is required and the investigator should communicate with the subject who has previously signed the ICF with the updated information, and obtain the written informed consent again. This process will also be documented.

With the consent of the subject, the investigator may inform relevant clinician of the subject's participation in the study.

